### Power calculation

Since this study is planned as a pilot study, formal statistical power calculations are not performed for all measures and tests of interest. The primary limitation for making power calculations is the lack of available information on what would constitute a clinically significant effect size for the measures of interest in OAT. Thus, we refer to other studies (regarding osteoarthritis of the knee and ultrasound therapy) for a “sample size calculation” since there is no justification with regard to statistical power [34, 35, 44]. The parameters determined with this pilot study will be used to plan the number of cases in a subsequent controlled prospective randomized trial. However, we estimated a sample size of 45 patients per group and defined a two-sided significance level of 0.05 for all tests. We expect a dropout rate of approximately 10% and therefore plan to enroll 50 patients per group, or a total of 150 patients.

### Data management

Each participant will be assigned a unique identifier upon study entry. This identifier will be used for all data documentation to assure the participant’s confidentiality. Data will be collected in source documents and then transferred onto paper case report forms. Later, all data will be digitized and stored in a central database. To improve the accuracy of data entry, entries will be verified for proper format and expected range as well as double-checked. Overall data quality will be assured by an independent monitor throughout the study. However, due to the minimal risks of our MHT and TUS interventions, an interim analysis or formal plan to stop the trial are deemed unnecessary. In terms of data and safety monitoring, a Safety Officer (SO) will be designated. The SO has no financial, scientific, or other conflict of interest with the trial. The SO meets with the Primary Investigator (PI) twice annually to review study progress, data quality, and participants’ safety. Data will be stored for 10 years after study completion and then deleted. Any modification to the current study protocol will be submitted to the institutional review board, to all trial participants, and to the trial investigators. On the consent form, participants will be asked if they agree to use of their data should they choose to withdraw from the trial. Participants will also be asked for permission for the research team to share relevant data with people from the universities taking part in the research or from regulatory authorities, where relevant. This trial does not involve collecting biological specimens for storage. Results will be explained to all study participants individually, presented at national and international conferences, published in peer-reviewed journals, and disseminated to surgeons, physio/hand therapists and the medical laity. We will comply with the official eligibility guidelines for authorship for all publications and do not intend to use professional writers.

### Data analysis

The data collected are described using statistical parameters. Continuous data are described with mean, standard deviation, minimum, maximum and 95% confidence intervals; for categorical data, the frequencies attained and the associated percentages are given with 95% confidence intervals.

The statistical analysis will only include the patients who complete the study in accordance with the protocol. Sub-collectives can be examined exploratively if this makes sense after the survey has been completed. In addition to the primary analysis of the comparison of patients with and without ultrasound therapy, there is a comparison of the patients between the different groups.

Group differences (MHT versus TUS versus study group with MHT + TUS) regarding the primary endpoint are analyzed with the non-parametric Kruskal-Wallis test for independent samples. After the global test, the groups are compared in pairs (Mann-Whitney tests). Secondary endpoints are evaluated according to the scaling of the data but are also always tested non-parametrically. The evaluation of intra-group differences (DASH or other characteristics after 9, 13, 17, and 33 weeks) is carried out by means of a nonparametric analysis of variance for repeated observations (Friedman test). In line with the nature of the pilot study, no adjustment is made for multiple testing. A *p* < 0.05 is considered (in the exploratory sense) to be statistically significant. Missing values will be replaced using multiple imputation [45]. All occurring AEs (AEs and SAEs) are described individually.

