
## Methods

### Study design

This is a single-center, randomized, controlled, repeated-measures, three-armed, parallel-group study conducted at the Waldfriede Hospital Berlin. Recruitment started in October 2019 (ClinicalTrials.gov identifier: NCT04115085). Patients are recruited from our hand surgery outpatient clinic on the Waldfriede Hospital campus. Further recruitment strategies include specific study calls on the website of the Waldfriede Hospital and information events and lectures for patients including distribution of study flyers. We intend to randomize 150 OAT patients to one of three hand therapeutic interventions. Intervention groups are (A) MHT with 18 sessions over 9 weeks, and (B) therapeutic TUS with 18 sessions over 9 weeks, and (C) combination therapy with MHT directly followed by TUS with 18 sessions over 9 weeks. Participants are studied on the first day before the intervention starts and at 9, 13, 17 and 33 weeks after the start of the intervention. The institutional review board of Waldfriede Hospital Berlin gave a positive evaluation for the study and written informed consent was obtained from all participants prior to study entry (Additional files 1 and 2). The study is conducted in accordance with the Declaration of Helsinki in its currently applicable version, the guidelines of the International Conference on Harmonization of Good Clinical Practice (ICH-GCP) and applicable German laws. Table 1 and Fig. 1 show the visit schedule and the study flow chart, respectively. Participants do not receive remuneration. For further details refer to the SPIRIT checklist (Additional file 2).

**Table 1 Tab1:** SPIRIT SUR study schedule

Visit	-1 Screening	0 Baseline Start intervention	1 End of intervention	2 Follow-Up	3 Follow-Up	4 Final follow-up visit
Week	−12 (max)	1	9	13	17	33
Informed consent	x					
Demographics	x					
Inclusion / exclusion criteria	x	x	x	x	x	x
Case history	x					
Medication	x	x	x	x	x	x
DASH		x	x	x	x	x
SF-36		x	x	x	x	x
VAS pain		x	x	x	x	x
Key pinch force		x	x	x	x	x
Goniometry		x	x	x	x	x
MHT		x	x			
TUS		x	x			
MHT + TUS		x	x			
Physical examination	x				x	
AE / SAE query		x	x	x	x	x

*AE* adverse event, *DASH* Disabilities of the Arm, Shoulder, and Hand, *MHT* multimodal hand therapy, *SAE* serious adverse event, *SF-36* Short Form 36, *SPIRIT* Standard Protocol Items: Recommendations for Interventional Trials, *SUR* Study of Medical Ultrasound for Rhizarthrosis, *TUS* therapeutic ultrasound, *VAS* visual analogue scale

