#### Complete list of exclusion criteria

History of surgery on the affected hand, wrist, or forearmPlanned surgery within the next 8 monthsAnticoagulation (Vitamin-K antagonists, heparin)Hemophilia, von Willebrand-Jürgens syndrome, thrombocytopathy, or other blood anomaliesAcute pain medication (< 7 days)Systemic medication with corticoids or immunosuppressantsIntra-articular injections or Radiosynoviorthesis (radiosynovectomy) (RSO) within the last 3 monthsPregnancy, lactationSignificant cognitive impairmentClinically relevant or progressive systemic disease (e.g., liver, kidney, cardiovascular system, respiratory tract, vascular system, brain, metabolism, thyroid) that could affect the course of the studyMalignant diseaseSimultaneous participation in an interventional study or participation in an interventional study in the last 2 months before study inclusionClinically relevant addiction or substance abuse disorder (defined as alcohol or drug abuse)Insufficient mental capacity to cooperateSuspected lack of complianceMedical, psychiatric or other conditions that restrict the patient’s following abilities: to interpret the study information, to give informed consent, to adhere to the rules of the protocol, or to complete the study

Discontinuation criteria are withdrawal of consent, subsequent occurrence of an exclusion criterion, lack of compliance, and medical reasons for stopping the intervention. Participants meeting a discontinuation criterion are offered the chance to attend the remaining study visits for follow-up outside the study protocol.

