## Discussion

Rhizarthrosis is a common and burdensome condition that causes substantial morbidity, disability, frequent ambulant health care visits, and hospitalization [5, 14]. Conservative therapies are needed because prevalence rates for osteoarthritis are rising and conservative treatment options have been scientifically underexplored [6, 19, 46]. Therapeutic exercise and manual hand therapy and their combination have been reported as effective methods to improve pain and function in short-term follow-up in OAT patients [20, 29, 47]. However, there is a body of evidence that TUS is an upcoming, highly effective, non-invasive, and time-sparing therapy in osteoarthritis. Recently, TUS was reported to improve pain, regeneration, and function in osteoarthritis of the knee [33–37, 48]. Despite these reports, no one, to the best of our knowledge, has studied TUS in OAT patients. To date, ours is the first study that investigates the efficacy of a 9-week intervention using MHT and TUS on patient-reported and disease-related measures in OAT patients, including a long-term period of follow-up over 6 months. We expect the findings from this trial to lead to new insights into the effectiveness and sustainability of manual therapy, ultrasound therapy, and a combination of both. OAT has been associated with more severe upper extremity disabilities as determined by DASH scores [49]. Consequently, we have chosen the DASH instrument as the primary outcome. In addition, we will assess objective measures, such as key pinch force and other disease-related and patient-reported outcomes, such as pain, health-related quality of life, and range of motion. There are several reasons for the lack of such large-scale, long-term studies. The predominant reason, of course, is the high demand of financial and human resources. Further, patients often prefer one particular intervention, and are thus apt to withdraw consent when randomized to an undesired intervention.

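### The efficacy analysis is limited to patients who complete per protocol, with no all-randomised population named, so exclusions after randomisation can bias the comparison of arms.

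*Protocol article*

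**What the plan says.** Under Data analysis, the protocol article sets one population: "The statistical analysis will only include the patients who complete the study in accordance with the protocol". No intention-to-treat or full analysis set appears anywhere in the article. The only other sets are undefined exploratory subsets. The same section adds: "Missing values will be replaced using multiple imputation".

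Under the exclusion criteria it says who stops: "Discontinuation criteria are withdrawal of consent, subsequent occurrence of an exclusion criterion, lack of compliance, and medical reasons for stopping the intervention". The exclusion criteria include planned surgery and recent intra-articular injection. In Table 1 (Study design), the row "Inclusion / exclusion criteria" is marked at every visit from screening to week 33. On later follow-up: "Participants meeting a discontinuation criterion are offered the chance to attend the remaining study visits for follow-up outside the study protocol".

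Under Data management, on the consent form, "participants will be asked if they agree to use of their data should they choose to withdraw from the trial". The Discussion remarks in general terms that patients often have a preferred treatment and are "apt to withdraw consent when randomized to an undesired intervention".

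**The concern.** Completing the study as planned is an event after randomisation. If the chance of completing depends on both the allocated arm and how the patient is doing, the completers in the three arms are no longer comparable groups, and the protection of randomisation is lost for the efficacy comparisons.

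Several features of the plan make such dependence plausible:

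- **Poor response can lead to exclusion.** A patient who does badly and is listed for surgery or given an injection meets an exclusion criterion, hence a discontinuation criterion, and leaves the analysis.
- **Patients know their arm.** The trial is open-label.
- **Burden differs.** Per hand and session, hand therapy takes 20 minutes plus daily home exercise, ultrasound takes 10 minutes, and the combination arm carries both.

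Two uses of the results are at stake. The Introduction aims at a direct efficacy comparison and at treatment recommendations. The Power calculation section says that the parameters found here will be used to size the next trial.

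**Working it through.** **1. The plan's own figure.** Inputs from Power calculation: 45 per group, about 10% dropout. 45 / (1 − 0.10) = 50 per group, and 3 × 50 = 150. This matches the plan. At that dropout, 3 × 45 = 135 patients are analysed, and 150 − 135 = 15 randomised patients are left out of the efficacy comparisons. No rate is given for exclusion through non-compliance, which would come on top.

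**2. Can the planned imputation repair this?** It can fill missed visits or items among completers. It cannot act on patients who are not in the analysis population. The two sentences do not strictly contradict each other, but imputation is kept away from the patients who stopped.

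**3. How large could the bias be?** The documents give no loss by arm and no link between loss and outcome, so the following are assumptions: two arms of 50, no true difference, normal outcome with SD 1. In each arm the worst fraction q leaves, ranked by a variable correlated ρ = 0.5 or 0.8 with outcome.

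The completer mean of an arm improves by ρ × m(q), where m(q) = φ(z₁₋q) / (1 − q). The between-arm bias is ρ × [m(q₁) − m(q₂)]. Values: m(0.04) = 0.090, m(0.06) = 0.127, m(0.10) = 0.195, m(0.14) = 0.259, m(0.16) = 0.290, m(0.20) = 0.350, m(0.30) = 0.497.

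The type I error of the two-sided 0.05 Mann-Whitney test comes from simulation (20,000 runs per row and ρ).

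| Loss, arm 1 / arm 2 | Mean loss | Bias in SD (ρ = 0.5 / 0.8) | Type I error (ρ = 0.5 / 0.8) |
|---|---|---|---|
| 10% / 10% | 10% | 0 / 0 | 5.6% / 6.7% |
| 14% / 6% | 10% | 0.07 / 0.11 | 6.8% / 9.7% |
| 16% / 4% | 10% | 0.10 / 0.16 | 8.2% / 12.9% |
| 20% / 6% | 13% | 0.11 / 0.18 | 8.7% / 15.6% |
| 30% / 10% | 20% | 0.15 / 0.24 | 10.7% / 23.3% |

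Example, 16%/4% with ρ = 0.8: 0.8 × (0.290 − 0.090) = 0.16. The simulated biases agree within about 0.01 SD, the smallest being 0.06 for 14%/6%.

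**4. The contrast that the plan calls primary.** Data analysis names patients with versus without ultrasound, that is, hand therapy alone against the other two arms together. With assumed losses of 20% (hand therapy), 6% (ultrasound) and 20% (combination), the bias is about 0.06 / 0.10 SD and the type I error about 7% / 11%. The effect is diluted because hand-therapy burden falls on both sides.

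**5. Equal loss.** With 10% outcome-related loss in each arm there is no between-arm bias, but the completer SD falls to about 0.96 (ρ = 0.5) or 0.91 (ρ = 0.8) of its true value. Required sample size scales with the variance: 1 − 0.96² = 0.08 and 1 − 0.91² = 0.17. A follow-on trial sized from these data would be about 8 to 17% too small.

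**The case against.** The strongest defence is that this is a pilot with p-values labelled exploratory, that a per-protocol set is legitimate, and that the analysis plan is not shown. The exploratory label does soften the type I error argument. It does not justify an avoidable selection, given the stated aims of comparing efficacy and suggesting treatment. A per-protocol set is sound as a supporting analysis, but here it is the only one. The word only makes this a fixed choice, which a later analysis plan could depart from only by contradicting the article.

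Some stronger readings are tempting but not supported:

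- **That treatment failures are dropped from every comparison.** Poor responders who complete per protocol stay in. Adverse events are described individually, with no stated restriction to completers.
- **That the authors forecast arm-dependent withdrawal in this trial.** The Discussion remark explains why such studies are lacking in general, and it concerns preference, not poor response. The only forecast is about 10% dropout, not split by arm.
- **That a type I error of up to 23% is to be expected.** The two highest-loss rows of the table assume a mean loss of 13% or 20%, above the stated 10%. Non-compliance could add to dropout, so they remain possible, but as upper scenarios.
- **That bias must favour a particular arm.** Every scenario assumes that the worst patients leave, which the documents do not establish.

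**Conclusion.** The concern holds for the efficacy comparisons. The plan limits them to protocol-compliant completers, offers no analysis of all randomised patients, and contains its own route by which poor outcome can lead to exclusion. Followed as written, it can bias the comparison of arms.

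The size is illustrative only. At the stated 10% mean dropout, unequal and outcome-related loss gives a bias of about 0.06 to 0.16 SD and a type I error of about 6.5 to 13%. Equal loss gives no between-arm bias but an SD that is too small for planning. Higher assumed losses give about 8 to 23%. These figures rest on the assumed splits, correlations of 0.5 to 0.8, and the worst patients leaving. The real direction and size cannot be known from the documents. The point should still be fixed, because the remedy is cheap and needs no knowledge of the size.

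**What to change.** - **Analysis population.** Replace the sentence in Data analysis with, for example: The primary analysis includes all randomised patients in the group to which they were allocated, regardless of completion or compliance. Missing DASH values are handled by multiple imputation (or a likelihood-based mixed model).
- **Sensitivity analysis.** Keep the protocol-compliant completers as a defined sensitivity set.
- **Data after discontinuation.** Reconcile the discontinuation paragraph, which places later visits outside the protocol, with the new population, so that outcomes from visits attended after discontinuation count as trial data where the consent described under Data management has been given. Changing the analysis sentence alone would leave these outcomes in doubt and put more weight on imputation. This concerns only the status of the data, not when treatment is stopped.

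**Cost.** Wording changes in two sections, one extra sensitivity table, and possibly a slightly smaller estimated effect. No extra patients: 150 are already planned, and at 10% dropout about 15 of them return to the comparisons.

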## Introduction

Rhizarthrosis (or osteoarthritis of the trapeziometacarpal joint) (OAT) is a common form of osteoarthritis in the hand leading to chronic disability in humans over 50. Although the exact mechanisms of osteoarthritis are still elusive, various person-level risk factors are recognized [1–9]. Although the hand X-ray is the gold standard for diagnosing and monitoring OAT, it has limited correlation to clinical symptoms [2, 10, 11]. The prevalence ranges between 4 and 36% depending on the diagnostic criteria used, rises sharply at ages over 60, and is thought to be twice to four times higher in women [2, 9–13] . OAT leads to articular cartilage damage, adjacent tissue degeneration, and may result in total joint destruction. Moreover, OAT is a major cause of progressive disability, early retirement, and depression in adults [8, 14, 15]. Currently, there is no cure for OAT, but several surgical therapies are available, with or without alloplastic reconstruction, which may improve function und reduce pain [16, 17]. However, they all may have substantial side effects, failure rates, and patients respond differently due to the complex nature of the disease. Therefore, conservative options should be considered first [18]. Consequently, there is a need for conservative therapies such as specific hand therapies that may reduce OAT symptoms, improve the patient’s quality of life, and, at best, delay disease progression [19]. It is unclear which conservative measures, if any, are most effective [20]. The aim of conservative treatment is to restore thumb functionality, including pain relief, stability, motility, and strength. Treatments commonly used prior to surgery include injections (cortisone, hyaluronate), analgesics, patient education in joint protection, strengthening exercises, assistive devices, and orthotics [21, 22]. Few randomized clinical trials on conservative treatment of OAT have been published [22–27]. There is increasing evidence favoring multimodal manual treatment to reduce pain and ameliorate function in OAT patients [26, 28–30]. For more than 60 years, therapeutic ultrasound (TUS) has been a non-invasive method to treat musculoskeletal pain, soft tissue injuries, and chronic wounds with debatable efficacy [31, 32]. However, recently TUS was reported to improve function, tissue regeneration, and relieve pain via thermal and non-thermal mechanisms in osteoarthritis of the knee [33–36]. Experimental data suggest that TUS treatment might prevent degenerative changes of the meniscus and exert a reparative effect via activation of cartilage growth factors [37]. Despite such evidence of efficacy, to the best of our knowledge, TUS has never been studied in OAT. Despite this lack of proven efficacy, based on our clinical experience, physiotherapists frequently use TUS to treat rhizarthrosis. It is of interest that TUS was used as a harmless, non-invasive ‘sham procedure’ in nontherapeutic doses in several clinical studies in OAT [20]. The aim of the present study is (1) to provide a direct comparison of the efficacy of two promising and readily available conservative treatment methods for symptomatic OAT, namely multimodal hand (MHT) therapy and TUS, (2) to suggest treatment recommendations, and (3) to offer direction for future studies. This research is expected to have a positive impact on OAT patients, because if MHT or TUS can reduce pain and improve function of the basal thumb joint, the significant disease burdens associated with pain and psycho-emotional stress, lost productivity, and frequent health care visits will also be reduced.

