### Outcome parameters

Primary outcome is the change in the disease-specific Disabilities of the Arm, Shoulder, and Hand (DASH) questionnaire score after 9, 13, 17, and 33 weeks compared to baseline [41, 42].

Secondary patient-reported outcomes include: (1) VAS pain determined by change in distance between the patient-made mark after 9, 13, 17, and 33 weeks compared to baseline; (2) Short Form 36 (SF-36) determined by scale score change after 9, 13, 17, and 33 weeks compared to baseline [43]. Secondary disease-related outcomes include: (3) Thumb force or key pinch force evaluation, determined by change in Kg after 9, 13, 17, and 33 weeks compared to baseline. All thumb force evaluations will be assessed in the following position: Thumb on top of the radial side of the index finger below. (4) Goniometry measurement determined by change in range of motion after 9, 13, 17, and 33 weeks compared to baseline. All goniometric evaluations assess the active range of motion (ROM) of the angle between the dorsal axis of the thumb and the index finger with a manual goniometer.

All clinical assessments will be performed by the same experienced evaluator at all time intervals, who is blinded to the treatment allocation.

For safety monitoring, patients will be asked for tolerability of the interventions and in case of AEs a medical doctor is always at our site to provide help. For a detailed overview of assessments and endpoints see Table 1.

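### The comparison named as primary sets two ultrasound arms against hand therapy alone, so it does not isolate the ultrasound effect and does not answer aim 1

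*Protocol article*

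**What the plan says.** Study design (protocol article) defines the first two arms as "A) MHT with 18 sessions over 9 weeks, and (B) therapeutic TUS with 18 sessions over 9 weeks" and the third as "C) combination therapy with MHT directly followed by TUS with 18 sessions over 9 weeks". No arm receives neither treatment.

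Data analysis introduces the between-group comparisons with "In addition to the primary analysis of the comparison of patients with and without ultrasound therapy", so the with/without-ultrasound contrast is primary and the comparison of the separate groups is additional. The next paragraph states: "Group differences (MHT versus TUS versus study group with MHT + TUS) regarding the primary endpoint are analyzed with the non-parametric Kruskal-Wallis test". It continues: "After the global test, the groups are compared in pairs (Mann-Whitney tests". No test is named for the with/without-ultrasound contrast itself.

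The section Outcome parameters gives the endpoint as follows: "Primary outcome is the change in the disease-specific Disabilities of the Arm, Shoulder, and Hand (DASH) questionnaire score after 9, 13, 17, and 33 weeks". The first aim in the Introduction is "to provide a direct comparison of the efficacy of two promising and readily available conservative treatment methods", namely MHT and TUS.

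**The concern.** A comparison described as ultrasound against no ultrasound will be read as the effect of ultrasound. Here the two sides also differ in hand therapy, which 100% of the no-ultrasound side receives and 50% of the ultrasound side. The imbalance comes from the arm definitions, so randomisation does not remove it, and the section describes no adjustment or stratification for hand therapy.

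If hand therapy works, part of its benefit counts against ultrasound. A useful ultrasound treatment can then look weak, null or even harmful in the result the plan calls primary. The Power calculation section intends the pilot's parameters to size a later trial, and the Introduction aims at treatment recommendations, so a distorted primary estimate could carry forward.

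**Working it through.** **Inputs from the protocol article.** The arm definitions are in Study design. The Power calculation section gives 45 evaluable patients per group, two-sided 0.05, 10% dropout and 50 enrolled per group. It gives no effect size, SD or power.

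**The plan's own figure.** 45 / (1 − 0.10) = 50 per group, and 3 × 50 = 150. This reproduces. The 45 itself cannot be re-derived and is taken as given.

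**What the contrast estimates.** Express effects as improvement relative to no treatment, with t for ultrasound, m for hand therapy and i for their interaction:

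- A = m
- B = t
- C = t + m + i

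With B and C of equal size:

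- (B + C)/2 − A = (t + t + m + i)/2 − m = **t − m/2 + i/2**
- C − A = t + i (ultrasound added to hand therapy)
- C − B = m + i (hand therapy added to ultrasound)
- A − B = m − t (the direct comparison of aim 1)

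The pooled contrast is the average of C − A and B − A: [(t + i) + (t − m)]/2. It therefore mixes an add-on question with a head-to-head question. It equals t only when m = i. With i = 0 it is zero when m = 2t and has the wrong sign when t > 0 and m > 2t.

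**Standard errors in SD units, 45 per arm.**

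- Pooled, 90 vs 45: √(1/45 + 1/90) = 0.183
- Pairwise, 45 vs 45: √(2/45) = 0.211
- Ratio: 0.211 / 0.183 = 1.155

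**Inert ultrasound (t = 0, i = 0).** By normal approximation, the chance of a significant result against ultrasound is Φ((m/2)/0.183 − 1.96). The values of m are assumed. The simulation used normal data and 4,000 runs per scenario.

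| m (SD) | Pooled contrast (SD) | Ultrasound significantly worse, normal approx. | Same, Mann-Whitney simulation | C vs A rejects, either direction, simulation |
|---|---|---|---|---|
| 0.3 | −0.15 | 13% | 12% | 4.8% |
| 0.5 | −0.25 | 28% | 25% | 4.3% |
| 0.8 | −0.40 | 59% | 52% | 5.0% |

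The nominal rate in that one direction is 2.5%.

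**Effective ultrasound (t = 0.5 SD).** Power in favour of ultrasound, by normal approximation:

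| m (SD) | i (SD) | Pooled contrast (SD) | Pooled power | C − A (SD) | C vs A power |
|---|---|---|---|---|---|
| 0 | 0 | 0.50 | 78% | 0.50 | 66% |
| 0.5 | 0 | 0.25 | 28% | 0.50 | 66% |
| 0.5 | −0.25 | 0.125 | 10% | 0.25 | 22% |
| 1.0 | 0 | 0 | 2.5% | 0.50 | 66% |

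The pooled contrast has the advantage in the first row, where hand therapy does nothing. In the second row the apparent effect is half the true one. If a later trial were sized on it, the required number would be (0.50/0.25)² = 4 times that for the true effect.

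Each rate refers to a single test of the endpoint at one time point.

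**The case against.** Several points on the other side stand.

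- **Valid comparisons are planned.** The pairwise Mann-Whitney tests cover A vs B, C vs A and C vs B. A reader might infer that the plan lacks a usable test of ultrasound, but it does not. The defect is the ranking.
- **Only one analysis is called primary.** A reader might infer that the with/without contrast and the Kruskal-Wallis test both claim that status. The Kruskal-Wallis sentence refers to the primary endpoint, which is an outcome, and the between-group comparison is expressly additional. What remains is that the only between-group tests named for the endpoint belong to the comparison ranked as additional.
- **The contrast is a legitimate randomised comparison** of ultrasound-containing regimens with hand therapy alone. The document never says that it estimates an isolated ultrasound effect, so calling it biased presupposes that target. It is still described by ultrasound alone, and it does not match aim 1.
- **The distortion is not simply −m/2.** That holds only without interaction, and arm C exists to study the combination. C vs A in turn gives t + i, not t.
- **No single rate can be put forward as the expected impact,** because the document supplies neither an SD nor a hand-therapy effect. Nor does it treat hand-therapy benefit as settled. The Discussion cites short-term reports of effectiveness, while the Introduction calls it unclear which conservative measures work best, if any.

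The trial is also labelled an exploratory pilot with no multiplicity adjustment. That lowers the weight of any p-value, but it does not justify a primary contrast that fails to match the stated question.

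**Conclusion.** The point holds in this form: the contrast named as primary is B+C versus A and estimates t − m/2 + i/2. It isolates ultrasound only if m = i, and it does not answer the first aim. This follows from the arm definitions (with B and C of equal size) and needs no outside figure.

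The size depends on assumptions. For an inert ultrasound treatment, no interaction, 45 evaluable per arm and a hand-therapy effect between 0.3 and 0.8 SD, a false finding against ultrasound would occur in about 13% to 59% of trials by normal approximation, or 12% to 52% by Mann-Whitney simulation. If hand therapy has no effect and there is no interaction, the distortion vanishes. The damage is limited by the planned pairwise tests, but as written they rank below the contrast that needs correcting.

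**What to change.** In Data analysis, drop the with/without-ultrasound contrast as primary or label it descriptive. Make the three-group comparison of the primary endpoint, already planned, the primary analysis, and state what each pairwise contrast is for:

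- A vs B: the named contrast for aim 1
- C vs A: the effect of ultrasound added to hand therapy (t + i)
- C vs B: the effect of hand therapy added to ultrasound (m + i)

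If the with/without contrast is kept as descriptive, say that its two sides differ in hand therapy and name the method used for it.

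**Cost.** Each pairwise contrast has a standard error about 15% larger than the pooled one. No new data, visits or patients are needed. The trial is recruiting, and under Data management a modification goes to the institutional review board, the participants and the investigators, so this is a formal protocol modification and not only an edit of the text.
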